## Abstract

**Background:**

With societal progress and a deepening understanding of Down syndrome (DS), research focus has shifted toward improving the quality of life and education for youth with DS. This study aims to determine the feasibility and estimate the preliminary effectiveness of a dyadic shared book reading program on the health-related quality of life of youth with DS (primary outcome), the mental wellbeing of university students (secondary outcome), and actor–partner outcomes to inform a future definitive trial.

**Methods:**

This study is an 8-week pilot dyadic randomized controlled trial (RCT) comparing a shared book reading intervention to a minimal activity control. The study will then continue for 12 months as a single-arm cohort study. Young people with DS and university students will be recruited, formed into dyads, and then randomized to either the intervention or control group. The intervention involves pairing a young person with DS with a university student for a weekly, 1-h shared book reading session. The control group will be provided with three books to read at their leisure over the 8 weeks. The primary outcome is the health-related quality of life of young people with DS, measured using the Pediatric Quality of Life Inventory (PedsQL 4.0). Secondary outcomes include the Engagement, Perseverance, Optimism, Connectedness, and Happiness (EPOCH) scale for measuring wellbeing. The Friendship Quality Questionnaire (FQQ) will be used to measure the dyad's level of friendship in the intervention group at 8 weeks. Measurements will be taken at baseline (T0) and at 8 weeks (T1). After 8 weeks, all participants will be offered the opportunity to continue in the study, joining the weekly shared book reading intervention; outcome measures will then be assessed at 6-month (T2) and 12-month (T3) follow-ups. Mixed linear regression models will be used to compare the intervention and control groups at 8 weeks. For the 6-month and 12-month follow-ups, change scores from baseline will be analyzed to test for potential long-term effect.

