### Study design

This study will be a pilot pragmatic parallel-group dyadic randomized controlled trial (RCT) comparing a shared book reading intervention (young people with DS paired with university student partners) to a minimal-activity control group.

All individuals with DS recruited into the study will be randomly paired with a university student to form a dyad. Depending on recruitment numbers, if more university students are enrolled than young people with DS, some dyads may consist of one participant with DS and two students (i.e., a 1:2 pairing). Each dyad will be randomized 1:1 to either the intervention group or the control group. Recruitment will take place over a 12-month period, with each participant involved in their assigned condition for 8 weeks. After this period, participants in the control group will also be offered the intervention. The primary outcome will be assessed at 8 weeks post- randomization. An extended phase will allow for exploration of long-term effects and sustainability, with outcomes measured at 6 and 12 months to inform future trial design.

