### Control group

Participants in the waitlist control group will be informed that they must wait 8 weeks before beginning the shared book reading sessions. Dyads in the control group will not be introduced during this 8-week period; participants with DS and students in this arm will only meet after the 8-week follow-up, when the intervention begins. To maintain engagement among youth with DS in the control group, they will be provided with three books to read independently or with their family during the waiting period. After the 8-week wait, control group participants will be invited to join the shared reading sessions. At that point, each young people with DS in the control group will be introduced to their student partner and may then participate fully in the weekly sessions. This approach ensures that while the control group receives books, they do not engage in dyadic shared reading until after the 8-week waitlist period. This design is methodologically critical, aligns with PPI group consensus that all participants eventually receive the intervention, and fulfills ethical requirements.

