### Outcome measures

Outcome measures will be collected at baseline (T0) and 8 weeks post-randomization (T1) for both the intervention and control groups. Following the initial 8-week RCT phase, all participants (including those from the waitlist control group) will receive the intervention; additional follow-ups will be conducted at 6 months (T2) and 12 months (T3) post-randomization in this single-arm extension phase. For the intervention group, outcomes for participants with DS will be collected at the end of the final session through researcher-administered interviews. For the control group, 8-week outcomes for participants with DS will be collected via researcher-conducted telephone interviews. University student participants in both groups will complete their outcome measures through an online survey, with reminder prompts sent after 1 and 2 days if not completed.

At T1, dyads in the intervention group will complete one additional measure (assessing the dyad's overall friendship) that will not be administered to the waitlist control group; all other outcome measurements are identical for both groups. The primary outcome of this study is the health-related quality of life of young people with DS at 8 weeks (T1), measured using the Pediatric Quality of Life Inventory (PedsQL)4.0. Secondary outcomes include the mental wellbeing of the student partners (assessed using the EPOCH scale) and the quality of the friendship within the dyad (assessed via the Friendship Quality Questionnaire, FQQ). Additionally, caregivers of participants with DS will complete a Global Perceived Effect (GPE) scale to evaluate their perception of change in the quality of life of the participant with DS.

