### Baseline characteristics

Baseline measurements will be recorded prior to randomization. Participant characteristics, including age, sex, height (cm), weight (kg), ethnicity, language, type of residence, and education level, will be collected. Caregiver information will also be recorded, including the caregiver's relationship to the participant and caregiver age. All outcome data collection points throughout the study timeline are presented in Table 1.

**Table 1 T1:** Data collection components and collection timeline.

**Construct**	**Outcome measure**	**Group**	**Baseline (T0)**	**8 weeks (T1)**	**6 months (T2)**	**12 months (T3)**
Socio-demographics		All participants	√	–	–	–
Health-related QoL	PedsQL 4.0	DS participants	√	√ (I+C)	√	√
		University students	√	√ (I+C)	√	√
Mental wellbeing	EPOCH	University students	√	√ (I+C)	√	√
Global perceived effect	GPE	DS caregivers	–	√ (I+C)	√	√
Friendship quality	FQQ	Intervention dyads only	–	√ (I)	√	√

DS, Young people with Down syndrome; I, Intervention group; C, Control group; PEDSQL 4.0, Pediatric Quality of Life Inventory version 4.0; EPOCH, Engagement, Perseverance, Optimism, Connectedness, and Happiness; GPE, The Global Perceived Effects scale; FQQ, Friendship Quality Questionnaire.

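### The planned test of a long-term effect at 6 and 12 months has no untreated comparator, so change from baseline should be described and not tested

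*Protocol article*

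**What the plan says.** The Abstract (Methods) describes an 8-week randomised comparison and then says "The study will then continue for 12 months as a single-arm cohort study". For the later visits it adds: "For the 6-month and 12-month follow-ups, change scores from baseline will be analyzed to test for potential long-term effect".

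Other sections fix the timing. Under Baseline characteristics: "Baseline measurements will be recorded prior to randomization". Under Control group: "Participants in the waitlist control group will be informed that they must wait 8 weeks before beginning the shared book reading sessions". Under Outcome measures, waitlist participants join the programme after the 8-week phase, and "additional follow-ups will be conducted at 6 months (T2) and 12 months (T3) post-randomization in this single-arm extension phase". T0 and the follow-up clock are therefore common to both arms, while the start of the sessions is not.

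The Study design section describes the purpose more modestly: "An extended phase will allow for exploration of long-term effects and sustainability". The Statistical analysis section sets out the 8-week comparisons and the actor–partner model. It names no comparison at 6 or 12 months.

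In Table 1, the Friendship Quality Questionnaire (FQQ) row is labelled "Intervention dyads only". It is marked for the intervention arm at T1 and carries ticks without an arm label at T2 and T3.

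**The concern.** A test of change from baseline asks whether the mean change differs from zero. It answers a question about the programme only if the mean would have stayed at zero without the programme. Nothing in the extension phase allows that to be checked, because no group remains untreated.

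Several other sources of change are plausible here. The participants with Down syndrome are 10 to 20 years old and will be followed for a year. Continuing after week 8 is by invitation, so those measured at T2 and T3 may be a selected group. Participants know what they receive, and the protocol itself says that this may shape expectations. A significant change score could come from any of these.

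The waitlist arm has a second, smaller problem. Its change from T0 includes the waiting period, so its change score does not measure change since starting the programme.

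At stake is what the pilot may say about durability, and what long-term effect size it passes on to the definitive trial.

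**Working it through.** The documents give no alpha, effect size or standard deviation for T2 or T3, so there is no figure of the plan's own to reproduce. The check has three parts.

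**1. Is there a comparator?** The Abstract and Outcome measures both call the phase single-arm, and both arms are offered the sessions after week 8. The only randomised contrast left at T2 and T3 is earlier against later start. The protocol does not plan that contrast, and it would estimate only the effect of starting 8 weeks sooner. No statement elsewhere could supply an untreated group.

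**2. How far is T0 from the start of the programme?** Inputs: T0 before randomisation (Baseline characteristics), an 8-week wait (Control group), T2 and T3 timed from randomisation (Outcome measures). Assumptions: 6 months = 26 weeks, 12 months = 52 weeks, and sessions begin at once in the intervention arm and at week 8 in the waitlist arm.

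| Visit | Weeks since start, intervention arm | Weeks since start, waitlist arm | Untreated share of waitlist change interval |
|---|---|---|---|
| T2 | 26 | 26 − 8 = 18 | 8/26 = 31% |
| T3 | 52 | 52 − 8 = 44 | 8/52 = 15% |

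The Abstract could also be read as 12 further months after week 8. The 8-week gap between the arms is the same on that reading.

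**3. What would drift do to the test?** This part is illustrative only. Assume a two-sided 5% one-sample t test on change scores, no programme effect, no drop-out, and a non-programme drift of d standard deviations of the change score. The rejection probability is P(|T| > t(0.975, n − 1)), where T is noncentral t with n − 1 degrees of freedom and noncentrality d√n. The sample-size sentence can be read as 12 dyads in all or 12 per group, so n = 12 and n = 24 are both shown.

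| Assumed drift d | n = 12 | n = 24 |
|---|---|---|
| 0 | 5% | 5% |
| 0.2 | 10% | 16% |
| 0.3 | 16% | 29% |
| 0.5 | 35% | 65% |

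None of the drift values, the alpha or the form of the test is in the documents. The table shows only the direction: any non-zero drift raises the rejection rate, and a larger sample raises it further.

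**The case against.** The best defence is that the protocol does not present this phase as confirmatory. It calls the phase single-arm openly, gives its purpose as exploration, and writes of a potential effect. The Statistical analysis section specifies no test at T2 or T3, and the limitations promise cautious interpretation. This lowers the weight of the point but does not remove it. The Abstract still says that the change scores will be used to test for an effect. The promised caution follows from the small sample, and a small-sample caveat does not deal with bias. The listed limitations mention neither the missing comparator nor the early baseline.

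Three stronger readings are tempting, and the documents do not support them.

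- **That the arms will be pooled at T2 and T3.** The single-arm label suggests it, but no sentence says so. Reporting by original arm may be set out in a fuller plan.
- **That friendship data will be lost from half the dyads.** The FQQ row label can be read that way. But the ticks at T2 and T3 carry no arm label, and Outcome measures withholds the questionnaire from the waitlist arm only at T1. By T2 the former waitlist dyads may count as intervention dyads. The row is ambiguous; a loss is not shown.
- **That the false-positive rate is known.** It depends wholly on an assumed drift and on full retention.

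It is also fair to object to simply moving the waitlist baseline to T1. That would give up the common pre-randomisation baseline and, with it, the early-versus-late contrast. For waitlist participants with Down syndrome, T1 is a telephone interview, whereas the intervention arm is interviewed at the final session, so a mode difference could enter. A T1 baseline would still supply no comparator.

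**Conclusion.** The point holds for the stated test. With no untreated group after week 8, change from T0 can be described but cannot test a long-term effect of the programme. This follows from the design as written and needs no numerical assumption.

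The baseline misalignment is secondary and concerns the waitlist arm only: 8 untreated weeks, about 31% of the interval to T2 and 15% of the interval to T3. These shares rest on 26- and 52-week visits timed from randomisation. The rejection rates are illustrative and carry no weight in the conclusion.

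The primary 8-week comparison is untouched. The matter is worth correcting because it decides what the pilot may claim about durability, and the correction is nearly free.

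**What to change.** 1. In the Abstract, replace the test at 6 and 12 months with a description: mean change from T0 with 95% confidence interval, by original arm, with no p-value and no claim of effectiveness. An interval that excludes zero is equivalent to a rejected test, so the statement that it is not evidence of effect must stand beside it. This brings the Abstract into line with the exploratory purpose in Study design.
2. Add the missing comparator at T2 and T3 to the limitations, separately from the small sample.
3. As a supplementary summary, report waitlist change from T1, which is already collected, and give time since first session. State that T1 is by telephone for waitlist participants with Down syndrome, and that this summary does not replace the one based on T0.
4. Reconcile the FQQ row of Table 1 with Outcome measures, so that it is clear whether former waitlist dyads complete the questionnaire at T2 and T3.

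The cost is wording, one table row and one extra summary, with no new visits. If item 4 is settled by including former waitlist dyads and this was not already intended, it adds one questionnaire at visits already planned. The downside is that the trial makes no formal long-term claim.

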**Discussion:**

This study focuses on the mental wellbeing of young people with DS and university students by promoting psychological health through shared book reading activities.

**Anticipated results:**

It is expected that the shared book reading activities will improve the mental wellbeing of both young people with DS and university students; however, due to the pilot study's sample size, this trial may not detect effectiveness at a level of statistical significance.

**Clinical Trial Registration:**

Clinicaltrials.gov, identifier NCT06813625.

## Introduction

Down syndrome (DS) is a congenital genetic disorder caused by chromosomal abnormalities (1). This condition can impact an individual's intellectual and physical development, leading to challenges in managing daily life and learning. Currently, the global incidence of DS is approximately 14 per 10,000 live births. This rate may vary across different sociocultural contexts due to disparities in access to genetic screening and attitudes toward pregnancy termination (2). In the United States, about 6,000 babies are born with DS each year, corresponding to an incidence of approximately 1 in every 700 births (3). In the UK, the prevalence is 12.6 per 10,000 live births, with around 750 babies born with DS annually (4). The incidence of DS among live births in China is notably lower, at 3.05 per 10,000 live births (5).

The impact of DS on individuals and their families is multifaceted. Individuals with DS often experience challenges in cognitive development, physical growth, and facial characteristic (6). These challenges can affect learning, language, and memory, and are also associated with increased health risks such as congenital heart disease, intestinal malformations, and vision or hearing impairments (7). Such physical and cognitive differences may impede the social development of a child with DS, who often struggles to form and maintain peer friendships. This can limit social wellbeing and emotional development, further reducing opportunities for social participation (8). A lack of social interaction has been strongly linked to lower quality of life, which is particularly evident in the DS population. Social engagement is crucial for quality of life in people with DS, as it not only provides a sense of fulfillment but also supports relationship-building and involvement in sports, hobbies, and other meaningful activities (9). Improving social engagement and quality of life for individuals with DS requires active support and acceptance from family, the community, and society as a whole.

Individuals with DS often demonstrate relative strengths in non-verbal learning, visual processing, and social skills, despite cognitive delays (10, 11). These strengths can be leveraged through social interventions such as shared book reading to promate engagement and learning. Shared book reading has been shown to positively influence the mental wellbeing of young people. Through reading and interactive discussion, youth can develop a deeper understanding of mental wellbeing concepts and increase their awareness of related issues. Additionally, shared book reading can stimulate enthusiasm for social interaction and make reading a more enjoyable experience (12). This activity may not only improve social participation and quality of life but also help young people better cope with challenges and achieve personal growth and development (13).

Although this is the first shared book reading intervention involving young people with DS and university students in Macau, previous studies on shared book reading have indicated positive outcomes. Research by Sun et al. (14) demonstrated that shared book reading can significantly improve emotional regulation and social skills in children, particularly among those with developmental disabilities. Similarly, another study found that shared book positively influences children's language development and mental wellbeing (15). Shared book reading involves interactive, paired reading accompanied by discussion and reflection. Although these studies focused primarily on school-aged children or individuals with other developmental conditions rather than specifically on DS, they suggest that shared reading can contribute to emotional and social benefits. Our study seeks to expand this evidence to young people with DS- a population that has not been studied in the context of such peer-interaction interventions. We hypothesize that shared book reading will not only improve mental wellbeing but may also enhance quality of life by promoting social engagement and emotional support, as indicated by existing literature.

Shared book reading may serve as an effective educational tool to help young people with DS improve language, cognitive, and social skills (16). By reading with others, young individuals can gain exposure to new knowledge and information, broaden their perspectives, and build self-confidence. Additionally, shared book reading can facilitate social and emotional exchanges among young people, their families, and peers, promoting mutual understanding and respect while contributing to a more inclusive and supportive environment (17). However, to date, there is a lack of research on shared book reading interventions that pair young people with DS with typically developing peers. This study aims to address that gap.

This study aims to pilot test the feasibility and evaluate the preliminary effects of a shared book reading intervention on the quality of life of young people with DS. The study also includes two secondary objectives:

**Secondary objective 1:** To examine whether shared book reading with young people with DS improves the mental wellbeing of participating university students.

**Secondary objective 2:** To investigate the actor–partner interdependence between young people with DS and their student partners in terms of quality of life and mental wellbeing outcomes.

## Methods

The study protocol has been developed and reported in accordance with the SPIRIT guidelines and follows the CONSORT 2025 flow diagram (Figure 1) (18).

**Figure 1 F1:**
[figure not shown]
CONSORT 2025 flow diagram.

### Patient and public involvement (PPI)

In recent years, PPI has gained widespread recognition in health-related research across many countries. However, adoption of this approach has been limited to date in China (19). PPI was incorporated into this study to ensure the relevance and appropriateness of the findings for young people with DS and their families. Throughout the development of the study, we involved young people, parents, caregivers, and public members in key discussions and decisions. The study was initially conceived and developed through PPI. The researchers, in collaboration with the Macau Down Syndrome Association (MDSA) organized two PPI meetings during the design phase of this study. The first meeting included researchers, young people with DS, their parents or guardians, and university students. During these sessions, researchers presented the concept of a shared book reading intervention involving university students and young people with DS, which received broad support. Several refinements were made based on PPI feedback regarding recruitment strategies, intervention length and content, outcome measures, and the location of intervention activities. A second meeting with MDSA representatives and parents/guardians led to further agreements on the management and scheduling of intervention activities. For example, weekends were preferred due to school commitments. In this meeting, PPI members also recommended incorporating engaging elements into the intervention to attract and sustain participant interest.

Through our co-design process, the PPI group played an active role in shaping the intervention, particularly in selecting and reviewing the reading materials, refining the intervention design, and defining the role of the supporters. The PPI group also served as key collaborators in identifying and selecting outcome measures for the study. The group will continue to provide mutual support, facilitated by the research team and the PPI lead. The PPI Advisory Panel will maintain close collaboration with the research team throughout the duration of the study.

